
#### Other Measures

Demographic and clinical variables such as age, gender, education level, work situation, duration of complaints, and possible comorbidities will be measured at baseline. Possible comorbidities will be measured again at 3 and 12 months after baseline to determine if patients have developed comorbidities or any chronic MUPS syndromes such as fibromyalgia, chronic fatigue syndrome, or irritable bowel syndrome.

### Sample Size

The number of eligible patients was calculated according to Campbell et al for cluster randomized trials [43]. The power calculation is based on an intracluster correlation coefficient of 0.04 [44,45] and a minimum of 20 patients per health care center. Additionally, we assume a minimal clinical detectable change of >10 points in the sum score of physical functioning of the RAND-36 questionnaire, and a SD of 23.8 [10]. Based on these assumptions and a power of 80% (alpha=.05), at least ten health care centers and 206 participating patients are needed. With an expected drop-out rate of 20%, a total of 248 participating patients (124 patients per arm) are needed for the study.

**Table 1 table1:** Summary of measures to be collected.

Outcome measures		Data collection instrument	Follow-up measurements				
			Baseline	3 months	6 months	9 months	12 months

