**Methods:**

This paper presents the study protocol of a multicenter cluster randomized clinical trial. Adult patients with moderate medically unexplained physical symptoms will be identified from electronic medical record data using the PRESUME screening method and proactively recruited for participation in the study. Cluster randomization will be performed at the level of the participating health care centers. In total 248 patients with moderate medically unexplained physical symptoms (124 patients per arm) are needed. The PARASOL intervention is a 12-week blended primary care program consisting of 4 face-to-face consultations with the mental health nurse and 5 physical therapy sessions, supplemented with a Web-based program. The Web-based program contains (1) information modules and videos on self-management and educative themes, (2) videos and instructions on prescribed home exercises, and (3) assignments to gradually increase the physical activity. The program is directed at patients’ perception of symptoms as well as modifiable prognostic risk factors for chronicity using therapeutic neuroscience education. It encourages self-management, as well as an active lifestyle using a cognitive behavioral approach and graded activity. Primary outcomes are impact of symptoms and quality of life. Secondary outcomes are severity of physical and psychosocial symptoms, general health, physical behavior, illness perceptions, self-efficacy, and cost-effectiveness. All measurements will be performed at baseline, 3 and 12 months after baseline. Retrospective cost questionnaires will also be sent at 6 and 9 months after baseline and these will be used for the cost-effectiveness analysis.

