### Randomization Procedure

Cluster randomization will be performed at the level of the participating health care centers. Health care centers will randomly be assigned to either the intervention group or the control group (usual care) using a Web-based random generation of a sequence of numbers. Through cluster randomization, we will avoid professionals within one health care center offering both the blended PARASOL intervention and usual care, as this could cause potential contamination effects [22]. A higher drop-out rate in the intervention group is expected since psychological therapies have a 7% higher proportion of drop outs compared with usual care [18]. The blended PARASOL intervention combines both mental health and physical therapy sessions. Therefore, an unequal randomization on cluster level will be conducted. Of the 15 included health care centers, 8 will be randomized to the blended PARASOL intervention and 7 will be randomized to the control group. After randomization of the health care centers, the selection and inclusion procedure of patients with moderate MUPS will be performed.

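### The 20% drop-out allowance was added as 206 × 1.2 rather than 206 / 0.8, so 248 recruits would leave about 198 completers, slightly fewer than the 206 the protocol requires

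*Protocol article*

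**What the plan says.** The Sample Size section of the protocol article bases the calculation on an "intracluster correlation coefficient of 0.04 [44,45] and a minimum of 20 patients per health care center", a "minimal clinical detectable change of >10 points in the sum score of physical functioning of the RAND-36 questionnaire", an SD of 23.8, 80% power and alpha 0.05. It concludes that "at least ten health care centers and 206 participating patients are needed". The next sentence makes the allowance for loss: "With an expected drop-out rate of 20%, a total of 248 participating patients (124 patients per arm) are needed for the study". The Methods part of the abstract repeats the total: "In total 248 patients with moderate medically unexplained physical symptoms (124 patients per arm) are needed". Neither place gives any other basis for going from 206 to 248.

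Two other statements bear on the per-arm figure. The Randomization Procedure section says: "A higher drop-out rate in the intervention group is expected since psychological therapies have a 7% higher proportion of drop outs". It gives this as the reason for unequal allocation of centres, of which "8 will be randomized to the blended PARASOL intervention and 7 will be randomized to the control group".

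**The concern.** The Sample Size section treats 206 as the number that must remain and 20% as the share of recruits who will be lost. If recruitment meets 248 exactly and drop-out is exactly as expected, the number remaining should then be at least 206. It is not. The total is stated in both the abstract and the methods, and readers will judge the finished trial against it. The Discussion already names recruiting enough patients for the desired power as a challenge, so no spare recruitment can be assumed to cover the gap.

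The equal figure of 124 per arm also raises a smaller question. More centres go to the intervention because more patients are expected to leave it, yet the patient target gives that arm no larger starting number.

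**Working it through.** **Inputs (Sample Size section):** required number 206; drop-out rate d = 0.20; stated total 248, or 124 per arm; difference 10; SD 23.8; intracluster correlation (ICC) 0.04; 20 patients per centre; power 80%; alpha 0.05, taken here as two-sided because the sidedness is not stated. **Randomization Procedure section:** 15 centres, split 8 and 7.

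**1. Reproducing 248.** N × (1 + d) = 206 × 1.2 = 247.2, rounded up to 248. Per arm, 103 × 1.2 = 123.6, rounded up to 124. Both stated figures are matched.

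**2. The number that retains 206.** N / (1 − d) = 206 / 0.8 = 257.5, rounded up to 258 (129 per arm). Check: 258 × 0.8 = 206.4.

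**3. What 248 leaves.** 248 × 0.8 = 198.4, about 198. The shortfall is 8 of 206, or 4%. The largest drop-out at which 248 still leaves 206 is (248 − 206) / 248 = 42 / 248 = 16.9%.

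**4. Power effect of this step, taking 206 as giving 80%.**
- The standardised effect at 80% power is 1.96 + 0.84 = 2.80.
- Simple scaling: 2.80 × √(198.4 / 206) = 2.75, which gives 78.5% power.
- With the number of centres held fixed, clusters shrink along with the total and the design effect falls, so power is about 79%.
- The loss is therefore about 1 to 1.5 points.

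**5. Does 206 follow from the stated inputs?**
- Individually randomised: 2 × (2.80 × 23.8 / 10)² ≈ 88.9, so 89 per arm.
- Design effect: 1 + (20 − 1) × 0.04 = 1.76.
- Total: 2 × 88.9 × 1.76 ≈ 313, or 314 after rounding up per arm. A t-based version gives about 317 and a one-sided version about 250. None of these is 206.

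**6. Power for 198 and 206 from the stated inputs with 15 equal centres.** Power = Φ(10 / SE − 1.96), where SE = 23.8 × √(4 × DE / N) and DE = 1 + (N/15 − 1) × 0.04.

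| Completers | Per centre | DE | SE | Power |
|---|---|---|---|---|
| 198 | 13.2 | 1.488 | 4.13 | 67.9% |
| 206 | 13.7 | 1.509 | 4.07 | 69.0% |

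With the 8:7 split carried to patients, the figures are 67.7% and 68.8%. With a t reference on 13 degrees of freedom (15 centres less 2), they are 61.1% and 62.2%. Each way, going from 206 to 198 costs about 1.1 points. These figures credit no gain from baseline or repeated measurements.

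**7. The per-arm figure.**
- 124 / 8 = 15.5 patients per intervention centre and 124 / 7 = 17.7 per control centre, so 124 and 124 can be reached with 8 and 7 centres.
- As an illustration, read the 7% as percentage points around a 20% average, giving 23.5% and 16.5% drop-out. This is an assumption. Then 124 + 124 leaves 94.9 and 103.5, with harmonic mean 99.0.
- A split proportional to centres, 132 + 116, leaves 101.0 and 96.9, with harmonic mean 98.9. The two are equivalent for power.

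**The case against.** The strongest reply concerns size, because the arithmetic itself is hard to dispute. One point of power is well inside the uncertainty of a planned drop-out rate, and 16.9% is not far from 20%. This stands, and it is why the point is a minor correction.

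A second reply is that the requirement of 206 was set with ten centres, while 15 are planned. At ICC 0.04, 206 patients in ten centres (20.6 each, design effect 1.784) carry an effective sample of 206 / 1.784 = 115.5. The 198.4 completers in 15 centres (13.2 each, design effect 1.489) carry 198.4 / 1.489 = 133.2. The planned layout therefore holds more information than the ten-centre requirement, even after the slip. This also stands. A reader might infer that the drop-out slip by itself makes the trial miss its stated power, and the documents do not support that. They do support the narrower statement that 248 does not leave 206 at the stated drop-out rate.

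A third reply is that missing values will be imputed by chained equations under intention to treat (Statistical Analysis section). This does not remove the point. Imputation does not fully restore lost outcome information, and the Sample Size section itself treats drop-out as needing extra recruits.

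A reader might also infer that 124 per arm contradicts the 8:7 allocation. It does not. The unequal randomisation is described as being at cluster level, no patient ratio of 8:7 is stated, and equal patient numbers are attainable. The 7% comes from psychological therapies in general and is not used in the sample-size text. The Discussion names drop-out in the control group as a challenge, which points the other way.

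**Conclusion.** The drop-out step is wrong as written. 248 is 206 × 1.2, and at 20% drop-out it leaves about 198 completers, 8 (4%) below the protocol's own 206. The number that retains 206 is 258. The arithmetic rests only on figures in the Sample Size section. The effect is small, about 1 to 1.5 points of power if 206 is accepted as giving 80%.

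Correcting this step should not be read as securing 80% power. The base of 206 does not reproduce from the stated difference, SD, ICC and cluster size, which give about 314 before drop-out on a two-sided test. That is a separate and larger matter, and it does not raise the weight of this point. It does mean that any power quoted for 198 must be computed afresh.

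The equal per-arm figure sits awkwardly with the reason given for randomising 8 and 7 centres. It needs a word of clarification, is not a contradiction, and has no material effect on power.

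**What to change.** Change the Sample Size section and the abstract in one of two ways.

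- **Keep 248.** State that about 198 completers are expected at 20% drop-out, and quote the power for 198 from the stated difference, SD, ICC and the 15 planned centres, with the sidedness of alpha given. Do not scale this power from 206. On the inputs as printed it is about 68% by the normal approximation and about 61% with a t reference on 13 degrees of freedom. This costs no patients.
- **State 258** as the number that retains 206 after 20% drop-out. This costs 10 more recruits, fewer than one per centre. It repairs the drop-out step only. If 206 is itself revised, divide the new figure by 0.8 in the same way.

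As a clarification, add one sentence saying whether equal patient numbers per arm are intended with 8 and 7 centres. No change to the allocation or to the arm sizes is called for on this ground.

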**Primary outcome measures**							
	Impact of symptoms^a^	Adequate Relief question	✓	✓			✓
	Quality of life	36-Item Short Form Health Survey (RAND-36)	✓	✓			✓
**Secondary outcome measures**							
	Pain	Numeric Rating Scale	✓	✓			✓
	Fatigue	Numeric Rating Scale	✓	✓			✓
	Severity of psychosocial symptoms	Four-Dimensional Symptom Questionnaire	✓	✓			✓
	General health	EuroQol-5 Dimensions	✓	✓			✓
	Physical behaviour	Activ8 activity monitor	✓	✓			✓
	Illness perceptions	Brief Illness Perception Questionnaire	✓	✓			✓
	Self-efficacy	Health Education Impact Questionnaire	✓	✓			✓
	Cost-effectiveness	Trimbos and iMTA questionnaire on Costs associated with Psychiatric illness	✓	✓	✓	✓	✓
	Barriers and facilitators of the blended e-Exercise health care program	System Usability Scale		✓			
**Other measures**							
	Age	Questionnaire	✓				
	Gender	Questionnaire	✓				
	Education level	Questionnaire	✓				
	Work situation	Questionnaire	✓				
	Duration of complaints	Questionnaire	✓				
	Possible comorbidities	Questionnaire	✓	✓			✓

^a^Measured weekly between baseline and 3 months follow-up, and monthly between 6 and 12 months follow-up.

### Statistical Analysis

Statistical analysis will be performed using IBM SPSS 22. Statistical analysis will be performed according to the intention-to-treat principle. Any missing values will be imputed with the Multivariate Imputation by Chained Equations. Descriptive statistics will be used to describe the number of patients with moderate MUPS (as identified using the PRESUME screening method) which are excluded by their GPs, how many patients are recruited with the 3 different strategies, as well as how many patients do not complete the blended PARASOL intervention. Additionally, descriptive statistics (frequencies, *t*-test and chi-square test) will be used to describe the demographic characteristics of the study population and to explore baseline comparability. Differences in effectiveness of the blended PARASOL intervention will be analyzed using longitudinal mixed methods analyses. In this way, we can correct for independence of observations within patients as well as take into account possible variations between clusters and health care professionals. Analyses will be corrected for potential confounders (eg, age, gender, and psychiatric comorbidity) and potential interactions terms (eg, age in the use of the Web-based component of the PARASOL intervention) will be checked. Furthermore, the cost-effectiveness of the blended PARASOL intervention will be clarified with an incremental cost-effectiveness ratio based on the costs per QALY. All costs measured by the TIC-P (health care use and indirect costs of illness and absenteeism) are used to calculate the incremental cost-effectiveness ratio.

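### Imputing every missing outcome ahead of the centre-level mixed model puts standard errors modestly at risk, in a direction that depends on how centre enters the imputation

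*Protocol article*

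**What the plan says.** All of the relevant text is in the protocol article.

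- **Imputation** (Statistical Analysis): "Any missing values will be imputed with the Multivariate Imputation by Chained Equations". No exception is made for outcomes. Nothing is said about the level of the imputation, its predictors or the role of centre.
- **Software** (same section): "Statistical analysis will be performed using IBM SPSS 22".
- **Analysis model** (same section): "Differences in effectiveness of the blended PARASOL intervention will be analyzed using longitudinal mixed methods analyses". This model is meant to "take into account possible variations between clusters and health care professionals". It is the only step in the section for which clustering is mentioned.
- **Design** (Randomization Procedure): "Cluster randomization will be performed at the level of the participating health care centers", and "Of the 15 included health care centers, 8 will be randomized to the blended PARASOL intervention and 7 will be randomized to the control group".
- **Planning values** (Sample Size): "The power calculation is based on an intracluster correlation coefficient of 0.04", at least 20 patients per centre, 20% drop-out and 248 patients in total.

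**The concern.** In a trial randomised by centre, the standard error of the treatment effect depends on how much centres differ. An imputation step can distort that quantity before the mixed model sees the data.

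- If imputed values are drawn without reference to centre, they pull each centre towards its arm's overall mean. The estimated between-centre variance shrinks and the standard error with it.
- If centre is entered as a set of fixed indicators, all imputed patients in a centre are drawn around that centre's noisy estimated mean. Sampling error is then read as true centre variation, and the standard error grows.

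With 15 centres the between-centre component matters, and missing data will not be trivial. The plan expects 20% drop-out and a higher rate in the intervention arm. The relief outcome also relies on weekly and then monthly answers. At stake are the width of the confidence intervals and the type I error for the primary outcomes.

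**Working it through.** The article gives no figure for the standard error after imputation, so there is nothing to reproduce first. The sample-size values serve here only as inputs.

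**Inputs from the article.** ICC = 0.04; missing share p = 0.20; 15 centres split 8:7, so 15 − 2 = 13 degrees of freedom; cluster size m = 248/15 = 16.5, or the stated minimum of 20.

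**Assumptions not in the article.** Data missing completely at random; correlation of 0.5 between baseline and follow-up; 10 imputations.

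**Step 1: formula, centre left out.** Variances are in units of σ²/n.

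- True variance with only the observed patients: [1 + (m(1−p) − 1)·ICC]/(1−p).
- The ICC in the completed data is about ICC·(1−p)² = 0.04 × 0.64 = 0.0256.
- Variance reported after multiple imputation: 1 + (m−1)·ICC·(1−p)² + p/(1−p).

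At m = 16.5:
- True: (1 + 12.23 × 0.04)/0.8 = 1.861.
- Reported: 1 + 15.53 × 0.0256 + 0.25 = 1.648.
- SE ratio: √(1.648/1.861) = 0.94.

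At m = 20:
- True: (1 + 15 × 0.04)/0.8 = 2.000.
- Reported: 1 + 19 × 0.0256 + 0.25 = 1.736.
- SE ratio: √(1.736/2.000) = 0.93.

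The standard error is thus 6 to 7% too small. With a normal reference the two-sided type I error would be 6.5 to 6.8%.

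**Step 2: simulation.** There were 2,000 trials per setting, with 8 and 7 centres of 16 to 17 patients and one follow-up outcome. Analysis was by random-intercept REML with Rubin's rules. The SE ratio is the root-mean-square reported SE over the empirical SD of the estimate. Rejection is on 13 df, with Monte Carlo error of about 0.5 points.

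| Setting | Method | SE ratio | Mean ICC | Rejection |
|---|---|---|---|---|
| ICC 0.04, 20% missing | Observed data, no imputation | 1.003 | 0.043 | 4.9% |
| | Imputed, centre omitted | 0.947 | 0.028 | 5.45% |
| | Imputed, centre fixed | 1.122 | 0.069 | 2.8% |
| ICC 0.04, 30% missing | Observed data, no imputation | 1.013 | 0.044 | 3.95% |
| | Imputed, centre omitted | 0.940 | 0.024 | 4.5% |
| | Imputed, centre fixed | 1.189 | 0.090 | 1.8% |
| ICC 0.10, 20% missing | Observed data, no imputation | 0.998 | 0.099 | 5.75% |
| | Imputed, centre omitted | 0.894 | 0.063 | 7.0% |
| | Imputed, centre fixed | 1.082 | 0.124 | 3.55% |

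With a normal reference at ICC 0.04 and 20% missing, rejection is 7.25% with centre omitted and 6.7% without imputation. Most of that excess over 5% comes from the small number of clusters, not from the imputation.

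**Step 3: a second simulation.** This used 10,000 trials and a t-test on centre means. With centre omitted at 20% missing, the mean reported SE was 0.1489 against a true SD of 0.1615, a ratio of 0.92. Rejection was 6.0%, against 5.3% without imputation. Part of the 8% shortfall belongs to the metric, because on 13 df the mean of a correct SE is already about 0.981 of the true SD. Corrected, 0.922/0.981 = 0.94, in line with Steps 1 and 2.

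**Step 4: a richer imputation model.** Letting the imputation of the 12-month value use the 3-month value moved the ratio from 0.93 to 0.97, with 4.7% rejection. This assumes a correlation of 0.7 between the two visits and values missing only at 12 months. The 3-month value brings some of the centre effect with it.

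**Step 5: repeat of the fixed-centre version.** In 4,000 trials at ICC 0.04 and 20% missing, standard errors were about 10% too large and rejection was 2.6%.

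**The case against.** The strongest objection is that the article never calls the imputation single-level. A reader might infer from the named software, and from the silence about centre, that the plan ignores centre, contradicts its own analysis model and so yields intervals that are too narrow. The documents do not support that. Chained equations can be single-level or multilevel, the predictors are not listed, and what SPSS 22 can impute is not in the documents. The details of an imputation model may also reasonably be left to a full protocol or analysis plan that is not shown. All of this stands, and it is why the point is conditional.

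A second objection is size. At the plan's own ICC and drop-out, the excess type I error with centre omitted is 0.55 to 0.7 points on 13 df (5.45% against 4.9%; 6.0% against 5.3%). The 0.55-point difference is about the size of the Monte Carlo error of that simulation. Using earlier outcomes as predictors reduces the effect further. The larger figures need an ICC of 0.10 or losses above 20%, neither of which is in the documents. This stands too.

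A third objection is that imputing before a mixed model is a legitimate choice. It can bring in information from variables outside the analysis model. That is true in general, but the article states no such purpose.

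What the objections do not remove is the stated rule itself: every missing value is imputed, outcomes included. Both simple ways of carrying that out in this design are miscalibrated, in opposite directions, whereas the mixed model on observed data is not.

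**Conclusion.** The point holds in conditional form. The article prescribes imputation of all missing values, outcomes included, ahead of a model that must account for centres, and it provides for clustering only in that model.

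- **Centre omitted:** standard errors about 3 to 7% too small at ICC 0.04 and 20% missing, with type I error about 5 to 6% on 13 df. The effect grows with the ICC and the amount of loss.
- **Centre as a fixed factor:** standard errors about 10 to 12% too large, so the test is conservative and power is lost.
- **No outcome imputation:** the mixed model on observed data has an SE ratio of about 0.98 to 1.00 across the runs at these planning values.

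The sizes rest on data missing completely at random, a baseline correlation of 0.5, and mostly on a single follow-up outcome rather than the full longitudinal model. The direction of any error in this trial cannot be known from the article. The effect is modest, but the better method is simpler than the stated one, so the change is worth making before analysis.

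**What to change.** Replace the blanket imputation sentence with two rules.

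1. **RAND-36 and the other repeated continuous outcomes:** fit the longitudinal mixed model, with its centre effect, to all observed data and do not impute outcomes.
2. **Where imputation is needed (weekly or monthly relief responder status, costs):** use a multilevel imputation model that includes arm, earlier outcomes and a random centre intercept. Fixed centre indicators are not an adequate substitute, for the reason shown above. Multilevel imputation was not itself simulated here; it is recommended because its structure matches that of the analysis model.

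The cost is a change of analysis wording before the data are analysed, with no effect on recruitment, measurement or conduct. Multilevel imputation may need a package other than the one named. Intervals may be slightly wider than under an imputation that ignores centre.

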#### Measurements

Three time points (baseline, 3-month, and 12-month follow-up) will be used for data collection. In addition, cost questionnaires will also be sent to the patients at 6 and 9 months. Furthermore, the impact of symptoms will be measured weekly between 0 and 3 months, followed by monthly measurements between 6 and 12 months. We offer no financial incentives to complete questionnaires or to carry the Acitv8 activity monitor. The measures that will be collected are listed below and Table 1 gives a summary of all measures that will be collected.

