Impact of symptoms, which addresses adequate relief using a validated single question, which is scored on a dichotomous scale (“Over the past week have you had adequate relief of your symptoms?”) [27,28]. A responder for adequate short-term relief is defined as a patient who will report adequate relief of their symptoms for at least six of the twelve weeks between the baseline and three-month follow-up. In addition, a responder for adequate long-term relief will report adequate relief of their symptoms for at least three of the six months between the 6- and 12-month follow-up. Otherwise, a patient will be defined as a nonresponder. Adequate relief is a validated clinically relevant endpoint and is defined at the point where the individual patient is satisfied with treatment [29].Quality of life will be measured with the 36-Item Short Form Health Survey (RAND-36) health survey. The RAND-36 is a valid and reliable self-reported questionnaire [30]. The questionnaire consists of eight subscales, namely physical functioning, social functioning, role-physical or emotional problems, mental health, vitality, bodily pain, and general health. A higher score on the scale of 0-100 indicates a better quality of life [30,31].Severity of symptoms, defined as self-perceived pain and fatigue in the past week, will be measured with an 11-point numeric scale (score 0-10) [32].Severity of psychosocial symptoms will be measured with the Four-Dimensional Symptom Questionnaire (4DSQ) questionnaire. This questionnaire consists of 4 subscales, namely distress, depression, anxiety, and somatization [33,34].Self-perceived health will be measured with the EuroQol-5D (EQ5D) questionnaire. This questionnaire will measure the perceived health on five levels (ie, mobility, self-care, usual activities, pain/discomfort, and anxiety/depression) [35].Physical movement behavior will be measured with the Activ8 activity monitor [36]. The Activ8 is a validated activity monitor to measure physical behavior by measuring several activities and postures (lying, sitting, standing, walking, running, and cycling). Patients will wear the Activ8 activity monitor for 1 week at varying intervals during the study. They will wear it at baseline, at 3 months follow-up, and at 12 months follow-up.Illness perceptions will be measured using the Brief Illness Perception Questionnaire. This questionnaire is an eight-item scale designed to assess cognitive and emotional representations of illness on an ordinal scale (0-10) [37,38].Self-efficacy will be measured with the Hei-Q questionnaire, which is a user friendly, valid, and reliable questionnaire specifically developed to evaluate patients’ education and self-management programs for patients with chronic complaints [39].Health care use and indirect costs through illness and absenteeism will be measured with Trimbos/iMTA Questionnaire for Costs associated with Psychiatric Illness (TIC-P) questionnaire to evaluate the cost-effectiveness of the program in terms of costs per Quality Adjusted Life Years (QALYs) [40]. Patients will be asked to complete the cost questionnaire every 3 months, since this questionnaire focuses on health-related costs in the past 3 months. QALYs will be measured using the EQ-5D scores [41]. In this way, we will get information of patients’ healthcare utilization and (unpaid) productivity losses.Besides the above parameters, the efficacy, barriers, and facilitators of the Web-based component of the blended PARASOL intervention from a patient’s perspective will be measured using the System Usability Scale (SUS). The SUS will be completed by patients of the intervention group at the end of the health care program (3-month follow-up). The questionnaire will measure the perceived usability by ten statements which can be scored on a 5-point Likert scale (‘totally agree’ to ‘totally disagree’). The SUS is a simple, valid, and reliable measurement and is often used the evaluate the usability of eHealth applications [42].

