## Results

The components of this intervention are based on results of a literature search and focus groups with experts (general practitioners, physical therapists, mental health nurses, and psychologists) [46]**.** The content of the information, self-management, and exercise modules were specifically developed for the current study. The functionality of the online program used in this study is based on the blended exercise intervention for patients with hip or knee osteoarthritis (e-Exercise) [47].

Before the start of the intervention program, physical therapists and mental health nurses of the experimental health care centers received two days of training on the content of the blended PARASOL intervention. The training consisted of presentations on the study population, central sensitization, therapeutic neuroscience education, graded activity, and perpetuating factors for all professionals involved in the study. Furthermore, the training included discussion of the content of the online modules and instructions on their implementation. During the study, a follow-up training session for the therapists will be conducted to ensure adherence to the treatment protocol.

The recruitment of health care centers started in June 2016 and inclusion of patients began in March 2017. Follow-up assessments of patients are expected to be completed in March 2019.

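### Cost per QALY rests on utilities at 0, 3 and 12 months although cost forms also go out at 6 and 9 months, and no source is named for platform and training costs

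*Protocol article*

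**What the plan says.** **Utilities.** Measurements states that "QALYs will be measured using the EQ-5D scores". In Table 1 the EuroQol row is ticked at baseline, 3 and 12 months only, in line with the three general data-collection points in Measurements.

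**Costs.** Measurements adds that "cost questionnaires will also be sent to the patients at 6 and 9 months", and Table 1 ticks the TIC-P at baseline, 3, 6, 9 and 12 months. The abstract gives the purpose: "Retrospective cost questionnaires will also be sent at 6 and 9 months after baseline and these will be used for the cost-effectiveness analysis". The three-monthly spacing is justified by the recall period, "since this questionnaire focuses on health-related costs in the past 3 months".

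**The ratio.** Statistical Analysis defines an incremental cost-effectiveness ratio per QALY and says: "All costs measured by the TIC-P (health care use and indirect costs of illness and absenteeism) are used to calculate the incremental cost-effectiveness ratio". No other cost source is named.

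**Programme inputs outside a patient questionnaire.** The programme includes a Web-based component. According to Results, physical therapists and mental health nurses in the experimental centers "received two days of training on the content of the blended PARASOL intervention", and a follow-up training session is planned.

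**The concern.** Costs are followed quarter by quarter, but utility has no reading between month 3 and month 12. The 3-month reading coincides with the end of the 12-week programme. Whether its benefit then persists or fades is what the economic comparison most needs to know, and a straight line across those nine months assumes the answer. The Discussion itself notes that moving from adopting a change to maintaining it takes at least six months, so the unmeasured stretch is where maintenance or relapse is expected. An analysis plan can state the interpolation, but it cannot supply readings that were never taken.

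On the cost side, a patient form on health care use and absenteeism would not, by its description, pick up the Web platform or staff training. Both are spent only in the intervention arm, so a ratio built from the TIC-P alone understates the incremental cost.

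Cost-effectiveness is a secondary objective. It is also the protocol's own answer to the overtreatment worry raised in the Discussion.

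**Working it through.** The article gives no QALY, cost or ratio figure, so there is nothing to reproduce. All utility differences and euro amounts below are assumptions chosen to show size.

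**1. QALY weights.** The trapezoid rule is assumed, since the article does not name a method. Each interval of length *L* years gives *L*/2 to each of its end points.

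- Readings at 0, 3 and 12 months: the intervals are 0.25 and 0.75 years. The weights are 0.25/2 = 0.125 at baseline, 0.125 + 0.75/2 = 0.50 at 3 months, and 0.375 at 12 months.
- Readings at 0, 3, 6, 9 and 12 months: the weights are 0.125, 0.25, 0.25, 0.25 and 0.125.

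The unmeasured stretch is 9/12 = 75% of the horizon.

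**2. QALY difference under assumed paths.** The between-arm utility difference is 0 at baseline and 0.05 at 3 months. Errors are relative to the five-point value.

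| Path from 3 to 12 months | Three-point | Five-point | Error of three-point |
|---|---|---|---|
| Falls to 0.01 by month 6, stays there | 0.50×0.05 + 0.375×0.01 = 0.02875 | 0.25×0.05 + 0.25×0.01 + 0.25×0.01 + 0.125×0.01 = 0.01875 | 53% too high |
| Holds at 0.05 to month 9, then 0.01 | 0.02875 | 3×0.25×0.05 + 0.125×0.01 = 0.03875 | 26% too low |
| Falls to 0 by month 6, stays there | 0.50×0.05 = 0.0250 | 0.25×0.05 = 0.0125 | 100% too high |
| Holds at 0.05 to month 9, then 0 | 0.0250 | 3×0.25×0.05 = 0.0375 | 33% too low |
| Linear from 0.05 to 0 | 0.0250 | 0.0250 | none |
| Constant at 0.05 | 0.04375 | 0.04375 | none |

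In the first two rows the readings at 0, 3 and 12 months are identical, so the planned schedule cannot tell those paths apart. The same holds for rows three to five.

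**3. Costs outside the TIC-P.** If *p* is the uncounted platform and training cost per intervention patient and Δ*Q* the QALY difference, the ratio shifts by *p*/Δ*Q*. For assumed *p* of 100 to 300 euro and Δ*Q* of 0.02 to 0.03, the shift runs from 100/0.03 = 3,333 to 300/0.02 = 15,000 euro per QALY. Its direction is fixed, because these costs arise in one arm only.

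**4. Cost window.** With a 3-month look-back, the five TIC-P forms cover −3 to 0, 0 to 3, 3 to 6, 6 to 9 and 9 to 12 months. All five span 15 months; the four follow-up forms span exactly 12, matching the QALY horizon. If the baseline form were added in, an assumed true 12-month incremental cost of 500 euro with a pre-baseline difference of −200, 0 or +200 euro would become 300, 500 or 700 euro. With no pre-baseline difference, nothing changes.

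**The case against.** **The QALY error is conditional.** With linear change from 3 to 12 months the three-point value is exact. The erring paths are assumed, each puts a sharp drop inside one quarter, and their errors have opposite signs. This stands: a reader might infer that the denominator is certainly distorted, or biased toward PARASOL, and the documents support neither.

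**The article says *all* TIC-P costs, not *only*.** A reader might infer that programme costs are excluded altogether. They are not: the four nurse consultations and five physical therapy sessions are health care use, a category that the cost sentence includes. What is left without a named source is the platform and the training. A full health-economic plan may deal with these, and their per-patient value depends on how one-off spending is spread.

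**Screening.** A reader might count PRESUME screening as an omitted cost that flatters PARASOL. Patient selection describes it as a recruitment route in the participating practices, and it runs after all 15 centers are allocated. It therefore occurs in both arms, and omitting it does not favour one.

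**Baseline costs.** A reader might infer that pre-baseline costs are certainly summed. The bracket in the cost sentence lists cost categories, not time points, and a baseline form is commonly kept for adjustment. Inclusion of patients after center allocation makes a baseline imbalance possible, but does not establish one. The wording is open, not wrong.

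**Timing.** Inclusion began in March 2017 and 12-month follow-up was due to end in March 2019, so enrolment would close by about March 2018, before publication in May 2018. With even accrual over those 12 months, about 8/12 of patients would then be past month 6 and 5/12 past month 9. This limits what added readings can recover, but does not remove their value.

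**Conclusion.** The concern holds in two parts. The firmer one is the utility schedule, which the article fixes: no EQ-5D between months 3 and 12, although cost forms go to the same patients at 6 and 9 months for the same analysis. With a 0.05 gain at 3 months, the QALY difference ranges from 53% too high to 26% too low if the gain ends at 0.01, and from 100% too high to 33% too low if it ends at 0. It is exact if the path is linear. These sizes rest on assumed paths and on the trapezoid rule.

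The second is that the TIC-P is the only cost source named and would not be expected to capture platform and training costs. If the ratio is calculated as written, their omission favours PARASOL by an amount the article does not give.

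Which TIC-P windows enter the sum needs clarifying; it is not a demonstrated error. Overall this is a cheap improvement to a secondary objective and does not touch the primary outcomes.

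**What to change.** 1. Add the EQ-5D to the 6- and 9-month cost mailings for every patient who has not yet passed those points. For the others, impute the missing readings or keep the three-point QALY.
2. State the interpolation rule and run a sensitivity analysis on it, with early-fade and late-hold paths between months 3 and 12.
3. Add platform and training costs per patient to the intervention arm from project records, and state how one-off spending is spread.
4. Sum only the 3-, 6-, 9- and 12-month TIC-P forms, which cover months 0 to 12, and use the baseline TIC-P as a covariate.

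The cost is five extra items in two existing mailings, a minor amendment and some bookkeeping. The drawback is a mix of three- and five-point QALYs, because patients already past months 6 to 9 cannot supply the added readings. Items 2 to 4 need no new patient data and apply to everyone.
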